## Ethical Approval

The study proposal, protocol, informed consent form(s), recruitment materials, and all participant materials will be submitted to the Makerere University School of Medicine Research and Ethics Committee (SOM-REC) for review and approval. Permission to carry out the study will also be sought from the Clinical Epidemiology Unit of the School of Medicine, the Uganda National Council of Science and Technology (UNCST) and the Kampala Capital City Authority (KCCA). Participant's written consent/assent will be sought for ALWHA and HCPs.

***Inclusion of children:*** adolescents aged 14-19 years will be enrolled in the study, therefore minors <18 years of age will be included. Much as the study is considered to be of minimal risk to participants including minors, their written consent/assent will be obtained before enrolling into the study. The consolidated guidelines for the prevention and treatment of HIV in Uganda allow adolescents above 12 years to make personal consent for HIV testing and care. All participants will be given sufficient time to read the assent form in their language and to ask any questions.

***Special consideration:*** adolescents who may become pregnant during the study will be given additional psychosocial support on top of the intervention and standard of care. The team will have a standby counsellor to take care of such special needs.

## Confidentiality and Privacy

Given the private nature of the HIV status, confidentiality and privacy will be treated with utmost importance. To protect the identity of participants the use of identifiers such as names, birthdays, specific locations and other potentially participant-specific information that can reveal their identity to people outside the study will be prohibited. Participants will be assigned numbers rather than using names. Secondly, no personally identifiable information from the study will be released to any unauthorized third party and all research activities will be conducted in as private a setting as possible. All information obtained from the study will be recorded using study identification numbers and kept in encrypted computer folders. All computers used will be password-protected. Data collected will strictly be used for study/research purposes only.

## Consent procedure and documentation

All consent forms will be translated into the local language (Luganda) and back-translated into English to ensure the correct use of the language. Consent forms will be read aloud to participants by trained staff. The informed consent will describe the purpose of the study, all the procedures involved, and the risks and benefits of participation. Interviewers will ask participants to summarize the study and explain the reasons why they want to participate. Either a signature or a thumbprint (for those who cannot write) will be acceptable to confirm informed consent for participation in the study, in the case of written consent forms.

### Strategies for retaining participants in the trial

To be able to retain participants in the trial, the research team will be sending weekly short messages (sms) to participants as study reminders, emphasize benefits of completing sessions during the briefing, schedule sessions on days that are most convenient to participants, provide incentives such as transport refund and breakfast for every session and keep sessions interactive and interesting.

### Data Safety and Monitoring Committee (DSMC)

The DSMC will be composed of five independent members including; a psychologist, a physician, a statistician, an epidemiologist and an ethicist.

No investigator directly involved in the care of the subjects will be recruited as a member of the DSMC. All severe adverse events that occur will be notified to the DSMC. The DSMC will meet at midway, three-quarters of the study to ensure the scientific integrity of the study, adherence to the protocol and conduct an interim analysis. The interim analysis may be conducted at the halfway stage of the study or as deemed necessary by the DSMC. Depending on the number of interim analyses, adjustments for the multiple comparisons will be made. The interim analysis P value adjustment will be done using the conservative method of Bonferroni to cater for multiple testing and avoid type 1 errors.

Stopping rules to be applied to the proposed trial will include:

- 1.) Availability of new efficacious psychosocial intervention when the trial is still ongoing.
- 2.) When treatment hazards outweigh the benefits of the intervention.
- 3.) The presence of very strong evidence of a treatment difference with a very small P value.
- 4.) The futility of the study due to the failure to recruit the required number of participants.

The presence of any or combination of these listed criteria as guided by the DSMC will lead to the stopping of the trial.

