##### *Inclusion Criteria:*

Participant should be 15-19 years of age, diagnosed HIV positive, attending care at Kisenyi Kitebi health center for the last 6 months, on first or second line of treatment, can speak/understand

Luganda or English and willing to provide informed consent/assent. All records will be confirmed via clinic medical charts.

*Exclusion criteria:*

A participant will not be eligible to be part of the study if he/she plans to move out of the catchment area within six months, or if he/she is participating in another study related to HIV and care improvement.

*Sampling for sub-study two*

*Sample size*

The following assumptions are considered for determining the appropriate sample size for the quantitative study.

Assumptions:

$$N = 2 \frac{[Z\alpha + Z\beta]^2 S^2}{(\mu_1 - \mu_2)^2}$$

where:

$Z\alpha$  is standard normal value corresponding to level of significance

$Z\beta$  is standard normal value corresponding to power of the study

$\alpha$ =acceptable type 1 error

$\beta$ = type II error

$\mu_1$  is mean in control group and  $\mu_2$  is mean intervention

$\mu_1 - \mu_2$  =effect size (minimum meaningful difference between the means in the control and intervention groups)

$S$ =standard deviation of the outcome in the control group

$N$  is the sample size per group

$Z\alpha = 1.96$ ,  $Z\beta = 0.84$ ,  $\alpha = 0.05$  in 2 tails,  $\beta = 0.20$  (at 80% power).

Considering a study evaluating effectiveness of Acceptance and Commitment Therapy (ACT) on reducing the depressive symptomatology among Swedish and Australian adolescents (Livheim et.al, 2015), the difference in means of the post treatment RADS2 scores between the ACT arm and control arm was 4.09 while the standard deviation in the control arm was 5.13.

Substituting into the formula,

$$N = (2(1.96 + 0.84)^2 \times 5.13^2) / (4.09^2)$$

$$N = 25.1$$

N=26 participants in each group

If we consider a possible clustering in any of the two sites and a design effect of 2.0, the new minimum sample size is  $26 \times (2) = 52$ . If we consider a 10% loss to follow-up, the revised sample size will become  $(52 \times (1 / (1 - 0.10))) = 58$  participants. We, therefore, aim to recruit, **a total of 116 participants** at 80% power of detecting a mean difference of 4.09 or more in the intervention.

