## Schedule of activities

|                                                               | 1 st Month | 2 nd Month | 3 rd month | 4 th month | 5 th month | 6 th month | 7 th month | 8 th month | 9 th month | 10 th month | 11 th month |
|---------------------------------------------------------------|-----------------------|-----------------------|-----------------------|-----------------------|-----------------------|-----------------------|-----------------------|-----------------------|-----------------------|------------------------|------------------------|
| INTERVENTION AND CONTROL GOUPS                         |                       |                       |                       |                       |                       |                       |                       |                       |                       |                        |                        |
| Eligibility Screen                                            | x                     |                       |                       |                       |                       |                       |                       |                       |                       |                        |                        |
| Informed Consent                                              | x                     |                       |                       |                       |                       |                       |                       |                       |                       |                        |                        |
| Adapting and Exploring acceptability of the adapted ACT-DNA-V | x                     | X                     |                       |                       |                       |                       |                       |                       |                       |                        |                        |
| Recruiting for Quantitative study                             |                       |                       | X                     |                       |                       |                       |                       |                       |                       |                        |                        |

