| Baseline assessment                                           |                       |                       | X                     |                       |                       |                       |                       |                       |                       |                        |                        |
| Post intervention assessment                                  |                       |                       |                       |                       |                       | X                     |                       |                       |                       |                        |                        |
| Assessment at 4 months Follow                                 |                       |                       |                       |                       |                       |                       |                       |                       |                       |                        | x                      |
| INTERVENTION GROUP                                     |                       |                       |                       |                       |                       |                       |                       |                       |                       |                        |                        |
| Mindfulness and ACT                                           |                       |                       |                       | X                     |                       |                       |                       |                       |                       |                        |                        |
| The noticer-Increasing noticing skill                         |                       |                       |                       | x                     |                       |                       |                       |                       |                       |                        |                        |
| The advisor-Normalizing experiences                           |                       |                       |                       | X                     |                       |                       |                       |                       |                       |                        |                        |

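### DSMC interim tests come too late to spare enrolment or sessions, and the sample size makes no allowance for their Bonferroni adjustment, so power could fall to about 71% or 65%

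*Protocol*

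**What the plan says.** **Interim testing.** The protocol's Data Safety and Monitoring Committee section has the committee meet midway and at three-quarters of the study and carry out an interim analysis. On timing it says "The interim analysis may be conducted at the halfway stage of the study or as deemed necessary by the DSMC". On multiplicity it says "The interim analysis P value adjustment will be done using the conservative method of Bonferroni to cater for multiple testing", with the adjustment depending on how many interim analyses are done. One of the four stopping criteria is "The presence of very strong evidence of a treatment difference with a very small P value".

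**Timeline.** In the Schedule of activities, the row "Recruiting for Quantitative study" and the baseline assessment are marked in month 3 only. The six sessions are in months 4 and 5. The row "Post intervention assessment" is marked in month 6 only, and the follow-up assessment in month 11. The feasibility definition under Operational Definitions also plans recruitment within one month. The hypothesis concerns the post-intervention assessment. Table 2 sets targets for depression, anxiety and stigma both then and at follow-up.

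**Sample size.** The calculation uses two-sided alpha 0.05 in full and claims 116 participants "at 80% power of detecting a mean difference of 4.09 or more in the intervention". No interim look enters it.

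**The concern.** An interim between-arm test is worth its cost when it can end enrolment or treatment early. Here everyone is recruited within one month and finishes the sessions before the outcome is measured, so it is not clear what such a test could save. It could still do harm in two ways. A Bonferroni share for the looks may be taken from a final test that was sized at the full 0.05. And a stop on the P value could end the follow-up that Table 2 needs. The protocol itself fixes the meeting times, the adjustment method and the P-value criterion, so the mismatch with its own schedule and sample size is not a detail left to a later analysis plan.

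**Working it through.** **1. What data would each look hold?** Month k of the schedule covers elapsed time k−1 to k, so the month-6 assessment spans 5.0 to 6.0. The protocol does not say how midway is counted. The look falls at start + fraction × (end − start):

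| Clock | Elapsed months | Midway | Three-quarters |
|---|---|---|---|
| 9-month Study period | 0 to 9 | 4.5 | 6.75 |
| 11-month schedule | 0 to 11 | 5.5 | 8.25 |
| Trial part only, months 3–11 | 2 to 11 | 6.5 | 8.75 |

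- Midway: no outcome data on the first clock; none or part of the post-intervention data on the second (5.5 lies inside the assessment month); all of it on the third.
- Three-quarters: all post-intervention data on all three clocks, with only the month-11 follow-up pending.
- If the trial were counted only to the post-intervention assessment (2 to 6), the looks would fall at 4.0 and 5.0, before any outcome score.

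Recruitment ends with month 3 and sessions end with month 5. So on any clock, a look that holds outcome data comes after both.

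**2. Reproduce the sample size.** The inputs come from the Sample size section: "the difference in means of the post treatment RADS2 scores between the ACT arm and control arm was 4.09", and "the standard deviation in the control arm was 5.13"; z = 1.96 and 0.84.

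- N = 2 × (1.96 + 0.84)² × 5.13² / 4.09² = 24.67 per arm. The protocol prints 25.1 and uses 26.
- Design effect 2.0: 26 × 2 = 52. Ten per cent loss: 52 / 0.90 = 57.8, so 58 per arm and 116 in total, as stated.

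**3. Power of the final test if Bonferroni covers it.** After loss, 52 completers per arm divided by 2.0 leave 26 effective per arm. The noncentrality is 4.09 / (5.13 × √(2/26)) = 2.875. The normal approximation to power is Φ(2.875 − z), where z is the two-sided critical value. The t-test version uses 50 degrees of freedom.

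| Final alpha | z | Normal | t-test |
|---|---|---|---|
| 0.05 (no interim) | 1.960 | 82.0% | 80.5% |
| 0.05/2 = 0.025 (one interim) | 2.241 | 73.7% | 71.2% |
| 0.05/3 = 0.0167 (two interims) | 2.394 | 68.5% | 65.5% |

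Starting from exactly 80%, the normal calculation gives 71.2% and 65.8%.

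**4. Sensitivity.**

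- Without the design effect (52 independent completers per arm), t-test power is 98.1%, 96.2% and 94.7% at the three alphas.
- If the looks fell at half, or at half and three-quarters, of the outcome information, the chance of crossing at any look would be 73.6% or 70.0% by simulation, starting from 80%. Real early looks would therefore recover only part of the loss.

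**5. Size needed to keep 80% with the looks.** By the protocol's own route: 30 → 60 → 67 per arm, 134 in total, with one interim; 33 → 66 → 74 per arm, 148 in total, with two.

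**The case against.** **The power loss is conditional.** The text adjusts the interim P value and states no reduced level for the final test. The interim is optional, and a look without outcome data gives no test to count. All of this stands, so the loss is something that could happen, not something the plan fixes. But the stated aim is to avoid type I errors, and Bonferroni does that only if all tests share the alpha. An interim at 0.025 on partial data, with the final test left at 0.05, has an error bound of 0.025 + 0.05 = 0.075.

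**The design effect may not be real.** Participants are randomised individually, and without it power stays high. This also stands. Yet 2.0 is the protocol's own planning assumption, and its 80% claim rests on it.

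**Stronger readings that the documents do not support.**

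- A reader might infer that every look is either empty or complete. The clock is undefined, the 11-month midpoint falls inside the assessment month, and the follow-up is still pending at three-quarters.
- A reader might infer that the open number of looks pushes the type I error above 5%. The protocol gives no thresholds from which to compute this. An empty look adds nothing, and a look at the complete post-intervention data uses the same data as the final test.
- A reader might fault the lack of a numeric boundary. That detail may sit in an analysis plan that is not shown.

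**Removing the test is a choice.** Budgeting for the looks would also make the plan consistent. In addition, the criterion speaks of a treatment difference without direction, so deleting it also removes a P-value trigger for a difference favouring control.

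**Conclusion.** The point holds in a limited form. The planned between-arm interim tests do not fit the schedule, because none that holds outcome data can spare anyone enrolment or sessions. Once the post-intervention data are in, a stop could only end the follow-up. The sample size does not budget for the tests. If one or two looks are taken and Bonferroni reaches the final test, power could fall from 80% to about 71% or 65%. Those figures rest on the protocol's difference of 4.09, its SD of 5.13 and its design effect of 2.0. The timing conclusion does not depend on which clock is meant. The conflict between the 9-month study period and the 11-month schedule is separate and should be reconciled.

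**What to change.** - Remove the between-arm hypothesis test and the P-value stopping criterion from the DSMC's remit.
- Keep the committee's review of adverse events, recruitment, retention, data quality and fidelity, and leave the safety-related stopping criteria as they are.
- State that the final post-intervention analysis carries no interim adjustment and is tested at two-sided 0.05.
- If the interim tests are kept, fix their number and the final alpha, and restate the power at that alpha or enlarge the sample as in step 5 of the working.

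The first route costs only protocol and DSMC wording. Its downside is that no P-value-triggered stop remains in either direction; on this schedule, such a stop could only have ended the follow-up.

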### Community Engagement Plan

To be able to conduct research that can be beneficial to the intended community, stakeholder engagement will be prioritized. The study will commence with a formative stage that will involve adapting the protocol to the specific needs of the community. Two stakeholder workshops will be conducted. During the workshops, various stakeholders will provide feedback on the appropriateness of language, content, metaphors, and language in the ACT-DNA-v protocol. This feed back will be used to make adjustments to the protocol. We intend to use a deliberative community engagement approach where community members will be offered an opportunity to consider the protocol in depth, challenge each others opinions and reach an informed position on what is appropriate.

## COVID-19 Risk Management Plan

The study will be carried out at health centres that have standard operating procedures to be followed as a response to COVID-19. However, on top of the health centre SOPs, we shall take off temperatures before access to the training room, provide hand sanitiser and face masks to all participants, set up a hand washing point outside the premises, have sessions with smaller groups and work from a large training venue to maximize social distancing. In addition to these precautionary measures, it will be a requirement that both researchers and participants present their COVID-19 vaccination cards to the principal investigator ahead of the study.

## Publication Plan

The study will result in three publications:

- i) Exploring the acceptability of mindfulness and acceptance-based psychosocial support intervention among providers (HCPs) and users (ALWAH).
- ii) Assessing the feasibility of an adapted mindfulness and acceptance-based intervention used among ALWAH in Kampala.
- iii) Examining the potential of a mindfulness and acceptance-based intervention to reduce the experience of anxiety, depression and internalized stigma among ALWAH in Kampala.

